### **6. Principles of Statistical Analysis**

The primary analysis will be conducted in the modified intention-to-treat (mITT) population. Safety outcomes will be primarily reported for the safety population, while the per-protocol (PP) population will be used for sensitivity analyses.

#### **6.1. Confidence Intervals and p-values**

The statistical significance level will be defined as a one-sided alpha of 2.5% for non-inferiority testing. For clarity in interpretation, results will be presented with two-sided 95% confidence intervals.

### **7. Statistical Analysis**

#### **7.1. Screening**

A summary will be provided overall and by participating site, including the following variables: duration of recruitment (in days), number of patients screened, number of patients enrolled, enrollment rate (patients per day), number of screened but not enrolled patients, and reasons for non-enrollment.

#### **7.2. Follow-Up**

Patients will be followed for 12 months, with in-person visits scheduled at screening/enrollment, at the time of the index procedure, and during follow-up at 1, 6, and 12 months. The expected course of patient participation throughout the study is illustrated in the CONSORT flow diagram (**Figure 1**).

**Figure 1. CONSORT flow diagram**

[figure not shown]

### **7.3. Baseline Characteristics**

Information on participants' baseline characteristics will include age, sex, NYHA functional class, heart failure etiology, left ventricular ejection fraction, blood pressure, heart rate, BNP, NT-proBNP, QRS duration, and the percentage of patients using each class of medication. These data will be presented for the overall study population as well as separately for each treatment group. No statistical comparisons will be performed to avoid unnecessary hypothesis testing.

Demographic and clinical characteristics will be summarized by treatment group and for the total sample. Categorical variables will be reported as absolute numbers (n) and percentages (%), whereas continuous variables will be presented as mean and standard deviation (SD) or as median and interquartile ranges (IQR), based on the normality of data distribution.

### **7.4. Primary Outcome Analysis**

The primary outcome, an ordinal clinical endpoint related to heart failure, will be compared between groups using a mixed-effects proportional odds model. The model will include a random effect for recruiting site and will be adjusted for baseline left ventricular ejection fraction, sex, and age. The primary comparison will be based on the conditional effect of the intervention, interpreted as the effect averaged over the distribution of covariates included in the model. Participants who are lost to follow-up or have only vital status data available at 12 months, with no clinical outcome information after randomization, will be excluded from the primary outcome analysis. If a patient has no recorded clinical events (death, hospitalization, or urgent heart failure visit) but lacks an LVEF assessment within the specified time window, another LVEF measurement collected during follow-up will be used for imputation. If no LVEF data are available, the mean 12-month change in LVEF, pooled across both treatment groups, will be imputed.

The validity of the proportional odds assumption will be tested to support the interpretation of results. However, even if the assumption is not met, the primary outcome will still be analyzed using the proposed model, and the estimated odds ratio can be interpreted as a summary (average) effect across the ordinal scale (21). Analyses will be performed using the *rms* package in R (22).

The non-inferiority margin for conduction system pacing compared with biventricular pacing will be defined as an odds ratio  $<1.20$  for the upper bound of the confidence interval. If non-inferiority is demonstrated at the one-sided 2.5% significance level, superiority testing will be subsequently performed using the same model, preserving the overall alpha level.

### **7.5. Secondary Outcome Analysis**

#### *7.5.1. Economic Outcomes and Cost Analysis*

To estimate the key secondary endpoint, a cost-minimization analysis will be conducted comparing the mean total direct medical cost per patient in the conduction system pacing (CSP) group versus the biventricular pacing (BiVP) group. Cost data will be consolidated in a patient-level database. To address missing data, a hierarchical imputation strategy will be employed, applying different methods based on the relevance of each variable and the presumed cause of the data being missing.

Key cost-driving variables will include device costs, time variables of the hospital resource use (serving as a primary *proxy* for overall resource consumption and labor resource use during the index hospitalization for the procedure), and costs associated with outcomes of interest.

A tolerance of up to 10% missing data will be allowed for time variables related to hospital resource use. If this threshold is exceeded, multiple imputation using *predictive mean matching* will be applied, based on covariates: enrollment site, baseline LVEF, sex, age, treatment group, and crossover occurrence. We will assume that missing data for these variables occur randomly at the patient level. No missing data are expected for device costs or outcome-related costs. For other cost-related variables with >10% missing data, median imputation will be used, assuming low impact on total costs and, consequently, on mean costs per treatment arm.

The primary economic endpoint will be presented as the mean cost difference between treatment groups. A generalized linear model with a log-link and gamma distribution will be used to test for significance, alongside non-parametric bootstrapping with 1,000 resamples to derive 95% confidence intervals. This approach accounts for the expected right-skewed distribution of cost data. Model adjustments may be made based on the final distribution of cost data at the end of follow-up. Additionally, median and interquartile ranges for cost outcomes will be reported by treatment group. This analysis will be based on the modified intention-to-treat (mITT) population, and the time frame will correspond to the duration of follow-up in the study.

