### **4.5. Sample Size**

Assuming an incidence of all-cause mortality of 6.2% in both groups (based on the RAFT trial, which reported 20.8% over 40 months via linear extrapolation), a 1-year heart failure hospitalization rate of 5.85% (RAFT: 19.5% over 40 months), and a 1-year urgent visit rate for heart failure of 0.5% (DAPA-HF: 0.5 events per 100 patient-years), along with an estimated absolute increase in left ventricular ejection fraction (LVEF) of 16% in the intervention group versus 14% in the control group (a conservative estimate based on the His-Alternative study, which showed increases of 16% and 13%, respectively), and a standard deviation of 6.5 (based on values of 6 and 7 in each group from the same study), a sample size of 304 patients would be required to achieve 80% statistical power with a two-sided alpha of 5% (one-sided alpha of 2.5%) and a non-inferiority odds ratio bound  $<1.2$  for the upper limit of the 95% confidence interval, accounting for a 5% loss to follow-up (assumed to be non-informative dropouts for the purposes of sample size calculation).

Due to slower-than-anticipated enrollment and the publication of a meta-analysis during the conduct of the PhysioSync-HF trial (Gin et al., Heart Rhythm, 2023) showing a greater improvement in LVEF in the intervention group (2.70–5.18%) than the originally assumed 2%, the Steering Committee decided to recalculate the original sample size.

The updated calculation assumed a 3% difference in LVEF improvement between groups, favoring the intervention arm. Although the originally anticipated difference based on the His-Alternative study was also 3%, a more conservative estimate of 2% had been used in the initial sample size calculation due to limited available data at the time. With the revised assumptions, the required sample size was reduced from 304 to 180 patients, while preserving the non-inferiority margin of OR less than 1.2 for the upper bound of the confidence interval and 80% statistical power. All simulations were performed using 10,000 repetitions, as detailed in Appendix A.

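### Section 7.5.1 fills non-key cost variables with a single median although the endpoint is a difference in skewed means, and the cost-minimization label is not tied to the non-inferiority result

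*Combined protocol and SAP*

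**What the plan says.** Section 7.5.1 defines the target: "To estimate the key secondary endpoint, a cost-minimization analysis will be conducted comparing the mean total direct medical cost per patient". On the effect measure it says: "The primary economic endpoint will be presented as the mean cost difference between treatment groups". Significance is tested with a gamma model with log link, and 95% intervals come from 1,000 bootstrap resamples. On the reason for these methods: "This approach accounts for the expected right-skewed distribution of cost data".

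Missing cost data are handled in tiers:

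- Hospital time variables: "A tolerance of up to 10% missing data will be allowed for time variables related to hospital resource use". Above that level, multiple imputation by predictive mean matching is used, with site, baseline LVEF, sex, age, treatment group and crossover as covariates.
- Device and outcome-related costs: "No missing data are expected for device costs or outcome-related costs".
- Everything else: "For other cost-related variables with >10% missing data, median imputation will be used, assuming low impact on total costs". The same sentence extends the premise to the mean cost in each arm.

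The plan does not say whether the median is pooled or taken within arm. Section 7.10 lists no sensitivity analysis of this fill.

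Section 3.2 states cost superiority of conduction system pacing (CSP) over biventricular pacing (BiVP) as an objective without condition. In section 7.4, the only step that depends on non-inferiority is the superiority test of the primary outcome itself. Section 4.4.3 lists cost-effectiveness as exploratory, and no section gives a method for it.

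**The concern.** The imputation rule does not fit the estimand. A median is a reasonable typical value for a skewed variable, but the endpoint is a mean. Each filled patient receives a value that is on average too low, and every filled patient receives the same value (or the same value within arm). This has three consequences. The component's mean is biased downward. The arm difference is distorted, most clearly when the two arms have different amounts of missing data. The spread of the filled data is too small, so an interval that treats the filled values as observed is too narrow.

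The second issue concerns interpretation. A cost-minimization analysis compares costs alone because outcomes are taken to be equivalent. The plan applies the label whatever the primary result, and gives no alternative framing if non-inferiority is not shown. A reader of the trial report could then take the cost result as a saving at equal outcome when the trial had not established that.

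**Working it through.** **No figure to reproduce for costs.** The documents give no cost standard deviation, missing rate, cost share or power for this endpoint. The sizes below are illustrations under stated assumptions.

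**Bias in one component.** For a log-normal cost component with coefficient of variation CV, median/mean = 1/√(1 + CV²). Filling a fraction m with the median changes the component's mean by −m × (1 − median/mean), if data are missing completely at random.

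| CV (assumed) | median/mean | m = 10% | m = 20% | m = 30% | m = 40% |
|---|---|---|---|---|---|
| 0.5 | 0.894 | −1.1% | −2.1% | −3.2% | −4.2% |
| 1 | 0.707 | −2.9% | −5.9% | −8.8% | −11.7% |
| 1.5 | 0.555 | −4.5% | −8.9% | −13.4% | −17.8% |
| 2 | 0.447 | −5.5% | −11.1% | −16.6% | −22.1% |

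**Bias in the arm's total.** The endpoint is total cost, so the component bias must be multiplied by the component's share of the total (assumed).

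- Share 5%: from 0.05 × 0.15 × 0.293 = 0.22% (CV 1, 15% missing) to 0.05 × 0.30 × 0.553 = 0.83% (CV 2, 30% missing).
- Share 30%: from 0.30 × 0.15 × 0.293 = 1.32% to 0.30 × 0.30 × 0.553 = 4.98%.

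**Effect on the arm difference.** A simulation used 90 patients per arm (Appendix A), 4,000 repetitions, log-normal components with assumed means 1.0 (CSP) and 1.3 (BiVP), so a true difference of −0.30, and data missing completely at random. Intervals were the estimate ± 1.96 standard errors, treating filled values as observed. Results for CV 1:

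| Missing CSP / BiVP | Pooled median: difference, coverage | Arm median: difference, coverage |
|---|---|---|
| 20% / 20% | −0.24, 91% | −0.28, 90% |
| 10% / 30% | −0.17, 83% | −0.22, 86% |
| 30% / 10% | −0.31, 95% | −0.35, 92% |

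Complete data gave about −0.30 with about 95% coverage. With CV 1.5 the filled differences ranged from −0.14 to −0.37. Coverage was 85 to 93%, except for the pooled median at 30% / 10%, where it stayed near 95%.

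The estimated standard error was about 0.15 after filling against 0.17 with complete data, so the filled data appear more precise than having no missing values at all. With the arm median, the actual spread of the estimates was 0.173 to 0.177. With the pooled median it was about 0.155, so the loss of coverage there comes mainly from bias.

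The direction is not fixed. In these examples the fill works against the CSP cost claim when missingness is equal or higher in BiVP, and for it when missingness is higher in CSP.

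**The label.** Appendix A states 81.4% power at the 1.2 margin. An unadjusted proportional odds simulation with the same inputs (3,000 repetitions, 5% dropout) gave 81.7%, so the figure reproduces. On the plan's own assumptions, including a 3-point LVEF advantage for CSP, the chance of not showing non-inferiority is therefore 100 − 81.4 = 18.6%. The plan needs wording for that case.

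**The case against.** The plan's tiers follow the presumed importance of each variable. The median is confined to residual variables, and the plan considered the effect on mean costs and judged it small. If these variables are about 5% of total cost, that judgement is right to within 1% of an arm's mean in the range examined. The skew statement concerns cost data in general, not these variables in particular. All of this stands and limits the size of the point. It does not make the median the right fill for a mean, and the premise is neither supported nor tested.

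Four stronger readings are tempting, and the documents do not support them.

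- A reader might infer that the variables with the most missing data get medians. Hospital time variables above 10% missing, however incomplete, get multiple imputation.
- A reader might set "No missing data are expected for device costs or outcome-related costs" against the sample size in section 4.5, "accounting for a 5% loss to follow-up", and conclude that costs after loss count as zero. No section says so. The 5% is a planning allowance, and section 7.13 has sites contacted for missing data. What is absent is a fallback rule.
- A reader might infer that the bootstrap ignores imputation uncertainty, or that time variables with 10% or less missing are mishandled. Section 7.5.1 does not give these details, so neither can be asserted.
- A reader might want the cost test formally gated on the primary result. Whether CSP costs less can be answered whatever the clinical result, and Table 1 already shows the primary odds ratio and the cost difference together. Formal gating is therefore debatable. The narrower point about the label remains.

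**Conclusion.** The point holds in two limited parts.

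First, single median imputation of the non-key cost variables with more than 10% missing is inconsistent with a difference in means of data expected to be skewed. It biases component means downward, can distort the arm difference in either direction, and understates uncertainty. Its effect on an arm's total mean cannot be settled from the documents: about 0.2 to 0.8% if these variables are 5% of total cost, and about 1.3 to 5.0% if they are 30%. Both ranges assume log-normal components, CV 1 to 2, 15 to 30% missing, and data missing completely at random. It may prove immaterial, but the plan offers no way to show that.

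Second, the cost-minimization label presumes equivalent outcomes, and nothing ties it to the primary result. This is a gap in interpretation, not an error in the cost comparison. Both parts are worth correcting because the remedy is inexpensive and mostly in the plan already.

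**What to change.** Replace the median fill with the predictive-mean-matching multiple imputation already specified in section 7.5.1, applied to all incomplete cost variables. Keep treatment group in the imputation model, and add death, heart failure events and length of stay as predictors. State that the imputation is carried through the bootstrap, so that the interval reflects it. This also removes the open choice between a pooled and an arm-specific median.

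Add to sections 3.2 and 7.5.1 that the cost-minimization label and interpretation will be used only if non-inferiority is shown. Otherwise, report the cost difference and the effect difference side by side, each with its interval and without that label.

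The cost is SAP wording and modest programming, a slightly wider cost interval, and no cost-minimization conclusion if the primary outcome fails. The cost comparison itself can still be reported in that case.

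### Median filling of the residual cost variables does not suit an endpoint defined as a mean of skewed costs, and its assumed low impact is never tested

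*Combined protocol and SAP*

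**What the plan says.** Section 7.5.1 of the combined protocol and SAP defines the key secondary analysis as "comparing the mean total direct medical cost per patient in the conduction system pacing (CSP) group versus the biventricular pacing (BiVP) group", and adds: "The primary economic endpoint will be presented as the mean cost difference between treatment groups". Significance comes from a gamma generalized linear model with log link, and the 95% interval from a bootstrap of 1,000 resamples. The stated reason is skew: "This approach accounts for the expected right-skewed distribution of cost data".

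Missing cost data are handled in tiers:

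- **Device and outcome-related costs:** "No missing data are expected for device costs or outcome-related costs".
- **Hospital time variables:** "A tolerance of up to 10% missing data will be allowed for time variables related to hospital resource use". Above that, multiple imputation by predictive mean matching is used, with these covariates: "enrollment site, baseline LVEF, sex, age, treatment group, and crossover occurrence".
- **Everything else:** "For other cost-related variables with >10% missing data, median imputation will be used, assuming low impact on total costs". The full justification is "assuming low impact on total costs and, consequently, on mean costs per treatment arm".

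The section does not list the variables in the last tier, give their share of cost or set an upper limit on missingness. It does not say whether the median is pooled or taken by arm, or whether filling is repeated in each bootstrap resample.

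**The concern.** The target is a mean, the plan itself expects right skew, and the filling value is a statistic that sits below the mean under right skew. The rule also applies only once missingness passes 10%, where the choice of filling value matters most.

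Three consequences are possible for an affected component: its mean is understated, its difference between arms is distorted, and constants inserted for unknown values make the data look less variable than they are. All three feed into the arm means, the mean difference and its interval, which are the result on which superiority in cost is to be judged (section 3.2).

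Nothing elsewhere in the plan would reveal the problem. The complete-data refit in section 7.10 concerns the primary ordinal model only. The per-protocol and as-treated repeats change the population, not the imputation.

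**Working it through.** The documents give no cost standard deviation, missing rate, cost share or cost power, so there is no planned figure to reproduce.

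**Inputs.** From Appendix A: 180 patients, 90 per arm. Assumed: component CV 0.5 to 2; missing fraction m from 11% (just over the threshold) to 30%; share of total cost w from 5% to 30%; values missing completely at random.

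**Step 1: component mean.** Relative bias = −m × (1 − median/mean). For a log-normal component, median/mean = 1/√(1 + CV²). Gamma ratios come from gamma quantiles.

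| CV | Median/mean, log-normal | Median/mean, gamma | Bias at 11% missing, log-normal / gamma | Bias at 30% missing, log-normal / gamma |
|---|---|---|---|---|
| 0.5 | 0.894 | 0.918 | −1.2% / −0.9% | −3.2% / −2.5% |
| 1 | 0.707 | 0.693 | −3.2% / −3.4% | −8.8% / −9.2% |
| 1.5 | 0.555 | 0.407 | −4.9% / −6.5% | −13.4% / −17.8% |
| 2 | 0.447 | 0.175 | −6.1% / −9.1% | −16.6% / −24.8% |

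At CV 1 and 25% missing: 0.25 × (1 − 0.707) = 7.3% (log-normal) and 0.25 × (1 − 0.693) = 7.7% (gamma).

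**Step 2: total cost.** Multiply by w (log-normal):

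- w = 5%, CV 1, m = 11%: 0.05 × 0.11 × 0.293 = 0.16%
- w = 10%, CV 1, m = 20%: 0.10 × 0.20 × 0.293 = 0.59%
- w = 30%, CV 2, m = 30%: 0.30 × 0.30 × 0.553 = 5.0%

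Hence roughly 0.2–5% for CV 1 to 2. The limits are not hard. At CV 0.5 the low end falls to 0.05 × 1.16% = 0.06%. With a gamma component the extreme corner is 0.30 × 24.8% = 7.4%.

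**Step 3: arm difference within a component.** With equal missingness, a true difference is multiplied by about (1 − m) under a pooled median, or by about 1 − m(1 − median/mean) under arm medians. With no true difference and missing fractions m1 and m2, a false difference of about (m1 − m2) × (mean − median) appears, and the arm with more missing data looks cheaper. The formulas against 10,000 simulated trials (log-normal, 90 per arm):

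| True means | CV | Missing | Median | Formula | Simulated difference |
|---|---|---|---|---|---|
| 80 vs 100 | 1 | 20% / 20% | pooled | −20 × 0.80 = −16.0 | −16.0 |
| 80 vs 100 | 1 | 20% / 20% | by arm | −20 × (1 − 0.20 × 0.293) = −18.8 | −18.7 |
| 80 vs 100 | 1 | 30% / 30% | pooled | −20 × 0.70 = −14.0 | −14.0 |
| 80 vs 100 | 1 | 30% / 30% | by arm | −20 × (1 − 0.30 × 0.293) = −18.2 | −18.3 |
| 100 vs 100 | 1 | 30% / 10% | pooled | −0.20 × 29.3 = −5.9 | −6.0 |
| 100 vs 100 | 2 | 30% / 10% | pooled | −0.20 × 55.3 = −11.1 | −11.2 |

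With 15% vs 30% missing, the false difference is 0.15 × 0.293 = 4.4% of the component mean at CV 1 and 0.15 × 0.445 = 6.7% at CV 1.5.

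**Step 4: uncertainty.** With arm medians, CV 1 and 30% missing in both arms, the standard error computed as if filled values were observed averages 11.1. The estimate's actual standard deviation across simulated trials is 14.0, so the computed error is 11.1/14.0 = 79% of what it should be. With a pooled median the two nearly agree (11.2 vs 11.5), but around a difference already shrunk to −14.0. If the median were recomputed within each resample, the bootstrap would pick up this variability; the bias would remain.

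**The case against.** The strongest defence is that the median rule covers only a residual tier. The named cost drivers are handled otherwise: device and outcome costs are expected to be complete, and time variables above the threshold get multiple imputation that includes treatment group. Section 1 attributes the expected saving to procedure and equipment, which lie largely outside the median-filled tier. At an assumed 10% share, a false component difference of 4–7% is only 0.4–0.7% of total cost. The 5% figure needs a large share, strong skew and heavy missingness together, and a 30% share sits awkwardly with a residual tier. Skew is expected of cost data in general, not of every minor item. A pooled median with equal missingness pulls a genuine component saving toward zero, which is conservative for a superiority claim. A spurious difference needs unequal missingness, which nothing in the documents indicates, and section 7.13 commits the coordinating center to chasing missing values.

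Most of this stands, and it limits the point. A reader might infer that any cost variable above 10% missing is median-filled, or that the cost comparison as a whole is biased. The text of 7.5.1 contradicts the first, and without a cost share the documents cannot support the second. Nor do they support saying outright that the intervals will be too narrow, because the nesting of filling within the bootstrap is unstated.

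What does not stand is the rule itself. Its only support is an assumption without a figure, the plan contains no check of it, and a better method is already specified a few lines earlier in the same section.

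**Conclusion.** The point holds for the residual cost variables only. For any of them that is right-skewed, with values missing at random, the rule understates the component mean by about 7–8% at CV 1 and 25% missing. It shrinks a component's arm difference by about the missing fraction under a pooled median, and by less under arm medians. It can create a difference where missingness differs by arm. Uncertainty is understated if filled values are treated as observed.

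In total cost this comes to roughly 0.2–5% under assumed CVs, missing fractions and cost shares, none of which the documents supply. The low-impact assumption may well be right, but as written it is neither supported nor testable. The rule should be changed; confidence is moderate because the size at the level of the endpoint cannot be fixed from the documents.

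**What to change.** In section 7.5.1:

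1. Replace the median rule with the predictive-mean-matching multiple imputation already planned for the time variables, applied to all incomplete cost components with treatment group in the model. With about 90 patients per arm, treatment can enter as a covariate; separate models by arm are not required.
2. Sum components to total cost within each imputed data set.
3. State how imputation and bootstrap are nested so that imputation uncertainty reaches the 95% interval, for example by resampling patients first and imputing within each resample.
4. Add a sensitivity analysis of the cost imputation. List the residual variables with their missing fraction by arm and their share of total cost, so that readers can judge whether the impact was low.

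Listing the variables, saying whether the median is pooled or by arm, and adding a sensitivity analysis would be a lighter alternative. It would make the rule transparent but leave the mismatch with a mean endpoint in place. The full change costs SAP wording and a few more variables in an imputation model already planned. It needs no new data, and intervals may become slightly wider.
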